### 2.7. Statistical Analysis

All analyses will be carried out using the Intention to Treat (ITT) principle. The outcomes of the variables included will be expressed as the median [range]. We will assess the normality of the distributions with Kolmogorov–Smirnov’s test and graphical methods. We will select the non-parametric Mann–Whitney U-test to compare continuous variables because both aforementioned tests were suggestive of an abnormal distribution. Categorical variables will be assessed with the chi-square and Fisher’s exact test. All tests will be two-sided. Logistic regression analysis will be performed to determine the potential predictors of clinical pregnancy, miscarriage and live birth rates using the Enter method.

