### 2.5. Intended Comparisons and Outcomes

The primary outcome measures will be the frequency of LH secretory peaks during the administration of the GnRH antagonist according to the adopted frequency of blood sampling. A secretory peak of LH is defined as the increase at levels ≥ 10 IU/L. Progesterone elevation > 1 ng/mL any time during the ovarian stimulation period will be also evaluated. Secondary outcome measures will be ongoing clinical pregnancy (fetal heartbeat at ultrasound) and miscarriage rates. Other prespecified outcome parameters included the total dose of gonadotropins (FSH), the endometrial thickness at day of triggering, number of retrieved cumulus oocytes complexes (COCs), MII oocytes, transferred embryos, day of embryo transfer, biochemical pregnancy (positive β-hCG), multiple pregnancy, ectopic pregnancy and live birth rates. Maternal side effects from the use of both drugs will also be monitored, including ovarian hyperstimulation syndrome. Embryo quality for embryo transfer or cryopreservation will be assessed according to morphological criteria [20].

Our primary analysis will be performed to provide a direct comparison of the study and control groups. We will also carry out logistic regression analysis, inserting variables, including demographic and IVF cycle characteristics, in order to reveal potential independent predictors that could potentially contribute to the change in the primary outcomes and live birth rate.

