### 2.6. Calculation of Sample Size

The present trial will be based on a consecutive series of patients. The sample size will be calculated as follows: If there is a true difference in favor of the experimental treatment of 5% (20% vs. 15%), then 160 patients (80 per group in case of 1:1 enrollment) are required to be 80% sure that the upper limit of a one-sided 95% confidence interval (or equivalently a 90% two-sided confidence interval) will exclude a difference in favor of the standard/control group of more than 10%. According to a pre-decided pattern from all authors, a pilot study will proceed the full procedure; in that, a total of 50 study subjects will constitute the first cohort in a ratio of 1:1 in both groups.

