Finally, we admit that this is an observational study that will carry the associated biases a priori; as a result, no definite conclusion can be drawn. In contrast, we believe that this is a new theory that has to be proven step-by-step. We fully acknowledge the anxiety of both patients and clinicians for premature LH surges and ovulation; especially for the later, we came across a lot of negative beliefs and fear when we tried to recruit IVF centres for participation. Our further—and initial—aim, though, remains to conduct a proper RCT to prove or disprove the outlined theory, but to do so with some preliminary data in our hands.

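### Section 2.7 plans two-sided tests and median [range] but no between-group difference with a confidence interval, although the hypothesis is non-inferiority (minor)

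*Protocol article*

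**What the plan says.** Section 2.7 (Statistical Analysis) names one summary measure: "The outcomes of the variables included will be expressed as the median [range", closing the bracket after that word. It then plans a normality check and, already expecting non-normal data, continues: "We will select the non-parametric Mann–Whitney U-test to compare continuous variables". For the other type of variable it says that "Categorical variables will be assessed with the chi-square and Fisher"'s exact test will be used. All tests are two-sided. Logistic regression is planned to look for predictors. The section mentions neither an estimated group difference nor a confidence interval.

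Section 2.5 defines the outcomes. The primary one is an event frequency: "The primary outcome measures will be the frequency of LH secretory peaks during the administration of the GnRH antagonist". The next level is also binary: "Secondary outcome measures will be ongoing clinical pregnancy (fetal heartbeat at ultrasound) and miscarriage rates". The continuous and count outcomes include "the total dose of gonadotropins (FSH), the endometrial thickness at day of triggering, number of retrieved cumulus oocytes complexes (COCs), MII oocytes, transferred embryos".

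The last paragraph of the Introduction states the hypothesis as non-inferiority of FSH alone. Section 2.6 sizes the full study (160, 80 per group) so that a one-sided 95% confidence limit, or equivalently a two-sided 90% interval, excludes a difference of more than 10 points in favour of control. The same section starts with a pilot: "a total of 50 study subjects will constitute the first cohort in a ratio of 1:1 in both groups". The Discussion gives the further aim: "to conduct a proper RCT to prove or disprove the outlined theory, but to do so with some preliminary data in our hands".

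**The concern.** The hypothesis and the sample size rest on an interval for a difference between two proportions. The analysis section plans tests of no difference and a descriptive format, and does not mention that interval. A non-significant two-sided test is not evidence of non-inferiority, least of all with 25 per group. If the report followed section 2.7 as written, a large p-value could be taken to support FSH alone when the data are compatible with differences well beyond the study's own margin in either direction.

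A smaller matter concerns the continuous outcomes. The range depends on the two most extreme donors and widens with sample size. It is least stable for skewed data, which is what section 2.7 expects.

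**Working it through.** **1. The plan's own figure.** Inputs from section 2.6: rates 20% (experimental) and 15% (control), margin 10 points, one-sided alpha 5%, power 80%.

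n per group = [p1(1-p1) + p2(1-p2)] × (z0.95 + z0.80)² / (true difference + margin)²
= (0.16 + 0.1275) × (1.645 + 0.842)² / (0.05 + 0.10)²
= 79.0

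The plan states 80 per group, so the figure is reproduced (power at 80 per group is 80.4%). The design criterion is therefore a confidence limit for a risk difference. By the same formula, power at the pilot's 25 per group is 40%.

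**2. What a two-sided test and an interval would each show at 25 per group.** The counts are assumed, chosen close to the planning rates: 5/25 (20%) with FSH alone and 4/25 (16%) with antagonist.

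- Fisher's exact test, two-sided: p = 1.0.
- Difference: 20% - 16% = +4 points.
- 90% Wilson limits: 10.1% to 35.8% for 5/25, and 7.4% to 31.2% for 4/25.
- Newcombe 90% lower limit: 0.04 - √[(0.20 - 0.101)² + (0.312 - 0.16)²] = -0.142.
- Newcombe 90% upper limit: 0.04 + √[(0.358 - 0.20)² + (0.16 - 0.074)²] = +0.220.

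The 90% interval is -14.2 to +22.0 points (95%: -17.7 to +25.4). If the event is favourable (pregnancy), the lower limit passes -10. If it is unfavourable (LH peak), the upper limit passes +10. Either way a 10-point difference in favour of control is not excluded, and p = 1.0 does not show this.

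**3. Range against interquartile range for continuous outcomes.** The documents give no distribution, so the shapes below are assumed. Values come from simulation at n=25. CV is the coefficient of variation of the spread measure over repeated samples.

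| Assumed shape | CV of range | CV of interquartile range |
|---|---|---|
| Normal | 18% | 24% |
| Log-normal, log-SD 0.5 | 33% | 27% |
| Log-normal, log-SD 0.8 | 51% | 32% |

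From n=25 to n=80 the expected range rises from 3.93 to 4.85 SD under normality, and from 5.0 to 7.3 (about 45%) under log-SD 0.8. Under log-SD 0.8 the interquartile range barely moves (1.09 to 1.12). The case for the interquartile range thus depends on skew. Under normality the range is the more stable of the two at n=25.

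**The case against.** Much can be said for the plan, and several stronger readings of section 2.7 fail.

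- **Every binary outcome would be reported as 0 [0–1].** A reader might infer this, since the sentence carries no exception, and at n=25 a median [range] would read that way with probability 98.3% at a true rate of 15% and 99.6% at 20%. In context, however, the sentence leads into the normality check and the Mann–Whitney test. Section 2.5 speaks of a frequency and of rates, section 2.6 works in percentages, and chi-square and Fisher tests are computed from counts. Proportions will be produced. The sentence is loosely worded, and that part of the repair is clerical.
- **The range gives no usable spread.** This does not hold. Under normality, range/3.93 recovers the SD at n=25 without material bias, with a CV of 18% against 14.5% for the sample SD. Under log-SD 0.8 the figures are 51% and 41%. The range is less precise but not useless.
- **The pilot cannot supply planning data.** This does not follow. Section 2.6 uses two proportions and a margin, with no SD. The Discussion asks only for preliminary data, and the donor-level records remain whatever the table format.

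Two further objections bear on what is left. First, logistic regression does estimate effects. But it is planned to find predictors, and an odds ratio cannot be set directly against a 10-point margin. Second, interval methods are often left to an analysis plan, which is not shown. That is fair, and it is one reason why the point is minor. Still, section 2.7 does state the comparison, as two-sided tests, and that comparison does not match the criterion in section 2.6.

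**Conclusion.** The point holds as a minor one. As written, the group comparison in section 2.7 does not yield the quantity on which the non-inferiority hypothesis and section 2.6 rest: the difference with its confidence limit. At 25 per group the gap is material to interpretation. With the assumed 5/25 and 4/25, p = 1.0 sits beside a 90% interval from -14 to +22 points. Other counts would move the interval, but it would remain wide against a 10-point margin at event rates near the planning rates.

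The preference for the interquartile range over the range rests on the plan's own expectation of non-normal data and on an assumed degree of skew (51% against 32% at log-SD 0.8, 33% against 27% at log-SD 0.5). No test, sample size or collected variable is wrong on this account.

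**What to change.** Limit the summary sentence in section 2.7 to continuous variables and add the estimates. Suggested text:

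*Continuous variables will be summarised per group as median [interquartile range]; the Mann–Whitney test will be accompanied by the Hodges–Lehmann difference and its confidence interval. Binary outcomes will be reported as n/N (%) per group, with the difference between groups and its two-sided 90% confidence interval, as used in section 2.6.*

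A 95% interval may be added. The range can be kept beside the interquartile range if the authors want the extremes shown. Mean (SD) is optional.

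The cost is two sentences. No new data are needed, and the tests and sample size do not change. The intervals from the pilot will be wide, and showing that width is their purpose.

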### 2.2. Eligibility Criteria

The inclusion criteria of the study population are: healthy women between 21–32 years old with a BMI of 21 to 29 kg/m^2^ who wish to donate their oocytes; normal ovarian reserve tests; normal menstrual cycles of 26–32 days; absence of any hormonal treatment during the last three months before entering the study and absence of coagulation and/or autoimmune disorders.

The exclusion criteria include: use of other protocols towards oocyte retrieval, such as natural, or modified natural cycles; poor ovarian response according to the Bologna criteria [19]; history of endocrine or metabolic disorders, ovarian cystectomy or oophorectomy; women with a diagnosis of polycystic ovary syndrome; clinical and/or laboratory markers of hereditary or acquired thrombophilia that complied to the standard protocols of each Unit and non-hormonal medication for a serious medical condition.

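### Oocyte yield is compared only by an unadjusted rank test with median and range, so donor prognosis goes uncorrected in an open, non-randomised pilot of about 25 per arm and no between-arm estimate or interval is planned

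*Protocol article*

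**What the plan says.** Section 2.7 fixes the test for continuous variables: "We will select the non-parametric Mann–Whitney U-test to compare continuous variables". Results are summarised by median and range. No covariate, between-arm estimate or confidence interval is named for these variables.

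Section 2.5 lists "number of retrieved cumulus oocytes complexes (COCs), MII oocytes" among further prespecified parameters, after the primary outcomes (LH peaks, with progesterone elevation also evaluated) and the secondary outcomes (ongoing pregnancy and miscarriage). It describes the main analysis thus: "Our primary analysis will be performed to provide a direct comparison of the study and control groups".

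The only regression is logistic. Section 2.5 uses it to look for "potential independent predictors that could potentially contribute to the change in the primary outcomes and live birth rate". Section 2.7 says: "Logistic regression analysis will be performed to determine the potential predictors of clinical pregnancy, miscarriage and live birth rates using the Enter method". Neither statement reaches oocyte counts.

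Section 2.2 requires "normal ovarian reserve tests" for entry and limits age to 21–32 years, so some measure of reserve and the age of every donor are known before stimulation. Section 2.3 allocates donors 1:1 by the order in which they enter each unit, with patients and gynecologists aware of the regimen. Section 2.6 sets a first cohort of 50. The Discussion calls the study observational and says that a proper RCT is to follow, with preliminary data in hand.

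**The concern.** Yield is where harm from leaving out the antagonist could show. The Discussion says that premature ovulation is inhibited because it would cost the woman part of her oocyte yield, and that live birth after frozen transfer keeps rising up to more than 25 oocytes.

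Allocation by order of entry, with no blinding, does not protect the crude comparison from a systematic difference in donor prognosis. A lower-reserve group 1 could look like a drug effect, and a higher-reserve group 1 could hide a real loss. A p-value beside two medians with ranges also tells the planners of the RCT little: it gives no size of difference, no interval around it and no SD.

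**Working it through.** **The plan's own figure.** The only sample size stated is 160 (80 per group), for 20% versus 15%, a 10-point margin, one-sided 5% and 80% power. n per arm = [0.15×0.85 + 0.20×0.80] × (1.645 + 0.842)² / (0.05 + 0.10)² ≈ 79.0, so 158 in total, which agrees. That figure concerns a proportion. The article gives no sample size, SD or power for oocyte yield.

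**Inputs.** From the article: 50 donors at 1:1, so 25 per arm; two-sided tests. Assumed, because the article gives none: a 5% level, SD of 7 oocytes, a true loss of 4 (used for power only), and a correlation ρ between reserve marker and yield of 0.1 to 0.7.

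**Systematic imbalance.** If the arms differ by d SD in reserve, the crude difference in yield shifts by ρ × d SD. With d = 0.5 (assumed; the documents report no imbalance) and no true effect, 6,000 simulated studies per row give:

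| ρ | shift in SD | shift in oocytes (×7) | Mann–Whitney rejects | rank ANCOVA rejects |
|---|---|---|---|---|
| 0.3 | 0.15 | 1.05 | 8.7% | 5.6% |
| 0.5 | 0.25 | 1.75 | 13.1% | 5.6% |
| 0.7 | 0.35 | 2.45 | 20.1% | 5.3% |

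With d = 0.3, a normal approximation gives 6.2%, 8.3% and 11.5% for the crude comparison.

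**Precision.** The unadjusted 95% half-width is about 2.011 × 7 × √(2/25) = 3.98 oocytes (simulated mean 3.96). Adjusting for two covariates, the second assumed to add nothing beyond the first, multiplies it by about √(1−ρ²) × √(1 + 2/45) × (2.013/2.011). The middle term is the price of estimating two coefficients with 50 donors.

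| ρ | multiplier | simulated half-width, crude → adjusted |
|---|---|---|
| 0.1 | 1.018 | 3.96 → 4.02 |
| 0.2 | 1.002 | 3.95 → 3.96 |
| 0.3 | 0.976 | 3.96 → 3.86 |
| 0.5 | 0.886 | 3.97 → 3.52 |
| 0.7 | 0.731 | 3.96 → 2.89 |

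**Power for a loss of 4 oocytes** at ρ = 0.3 (same simulation): Mann–Whitney 49%, unadjusted t-test 52%, adjusted 53%. On normal data, most of the gap between Mann–Whitney and the adjusted model comes from the change of test, not from the covariates.

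**The case against.** A Mann–Whitney test with medians is a conventional and valid choice for skewed counts in a 50-donor pilot, and it copes with donors who yield no oocytes. Several further points stand.

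- **Rank.** Yield sits below the primary and secondary outcomes. A reader might infer that the trial's main conclusion is at risk; it is not.
- **Power.** A reader might infer that adjustment rescues an underpowered comparison. That needs ρ near 0.7. Section 2.2 admits only normal-reserve donors aged 21–32 and excludes polycystic ovary syndrome and poor responders, which narrows the covariate range and makes low ρ likelier. With skewed (lognormal) yield at ρ = 0.3, Mann–Whitney has 65% power and an adjusted linear model 66%.
- **Chance imbalance.** With 25 per arm, the difference in mean reserve has a standard error of √(2/25) = 0.28 SD. A reader might count this as bias on top of lost precision. It is sampling error, already covered by the crude test's error rate (simulated 4.2–5.2% with no systematic imbalance). Only a systematic imbalance is bias.
- **Available data.** Section 2.2 names no marker, assay or cut-off, and five units recruit. That all of them hold one common numeric value is not established.
- **What an article leaves out.** Intervals and supporting models could stand in a fuller plan that is not shown. This limits the complaint about the missing estimate. It does not remove the point about adjustment, because the article does name the method for these outcomes.

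It does not answer the concern to say that entry order is called random. The order is not concealed, treatment is open, and the Discussion itself expects observational bias.

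**Conclusion.** The concern holds in a limited form. As stated, the analysis of COCs and MII oocytes leaves measured donor prognosis uncorrected in a comparison whose allocation does not balance it, and gives no between-arm estimate or interval to carry into the RCT.

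The main benefit of a change is control of measured imbalance and a usable estimate; the latter does not depend on ρ. The precision benefit does: none or slightly negative at ρ of 0.2 or below, a 2–3% narrower interval at 0.3, about 11% at 0.5 and about 27% at 0.7, with the low end likelier. The error rates of 8.7% to 20.1% rest on an assumed 0.5 SD imbalance that the documents neither report nor exclude. Adjustment leaves unmeasured confounding in place.

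**What to change.** In section 2.7, add a prespecified adjusted comparison for COCs and for MII oocytes.

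- **Covariates:** arm, age, and one named numeric ovarian reserve marker that every recruiting unit already measures at screening. If there is no common marker, use age alone.
- **Model:** one that accommodates zero counts, such as negative binomial, proportional odds or rank ANCOVA. A linear model for log counts is undefined for a donor with no oocytes, which premature ovulation could produce.
- **Reporting:** the adjusted difference or ratio with its 95% CI, plus mean (SD) and median (IQR) by arm.
- **Mann–Whitney:** keep as a supporting analysis.

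The cost is a few sentences, a little analysis work and up to two degrees of freedom, after confirming with the units that a common marker exists. No extra donors or visits are needed if it does, or if age is used alone.

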The aim of this pilot study is to compare the efficacy of a protocol using FSH alone with that of a protocol using FSH plus a GnRH antagonist for COH in cycles of elective freezing in the context of a donor/recipient program. The hypothesis to be tested is that a COH protocol that includes FSH alone without any LH surge prevention regimens is not inferior to a protocol including FSH plus a GnRH antagonist in terms of clinical outcomes.

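### The study is sized for non-inferiority against a 10-point margin, but section 2.7 analyses categorical outcomes with tests of no difference and never uses the margin

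*Protocol article*

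**What the plan says.** The Introduction gives the hypothesis: FSH alone "is not inferior to a protocol including FSH plus a GnRH antagonist in terms of clinical outcomes". The Abstract says the same.

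Section 2.6 turns this into a design rule. With true rates of 20% and 15%, a difference favouring the experimental arm, 160 patients (80 per group) "are required to be 80% sure that the upper limit of a one-sided 95% confidence interval" (or the two-sided 90% interval) "will exclude a difference in favor of the standard/control group of more than 10" percent. A first cohort of 50, split 1:1, precedes the full study. The outcome behind the 20% and 15% is not named.

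Section 2.5 makes the frequency of LH secretory peaks primary, puts ongoing clinical pregnancy and miscarriage among the secondary outcomes, and describes the primary analysis only as a direct comparison of the groups.

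Section 2.7 then fixes the methods: "Categorical variables will be assessed with the chi-square" and Fisher's exact tests, and "All tests will be two-sided". It mentions no margin, risk difference, confidence interval or rule for concluding non-inferiority. The Discussion expects the results to show whether the two protocols have similar clinical efficacy.

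**The concern.** Sections 2.6 and 2.7 ask different questions of the same data. Section 2.6 asks whether a control advantage of more than 10 points can be ruled out. Section 2.7 asks whether the hypothesis of exactly equal rates can be rejected. A non-significant answer to the second leaves the first open, and in a study of this size non-significance is likely whether or not FSH alone is worse.

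This is a method that is stated and does not fit the hypothesis, rather than detail deferred to a fuller document. If section 2.7 is followed as written, the hypothesis for which the patients were counted is not tested, and the result most likely to be obtained is uninformative about it.

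**Working it through.** **1. What kind of sample size is it?** Inputs from section 2.6: rates 0.20 and 0.15, margin 0.10, one-sided 5%, power 80%.

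n per group = (z₀.₉₅ + z₀.₈₀)² × [p_E(1−p_E) + p_C(1−p_C)] / (margin + p_E − p_C)²

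= 6.1826 × (0.1600 + 0.1275) / (0.10 + 0.05)² = 6.1826 × 0.2875 / 0.0225 = 79.0.

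So 79 per group, or 158 in total, which agrees with the stated 80 and 160. Power at 80 per group is 80.4%. The figure is a non-inferiority size. A two-sided 5% test of no difference between 20% and 15% would need 906 per group at 80% power; that test has 12.9% power at 80 per group and 6.7% at 25 per group.

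**2. Can the two sections disagree on one data set?** Take a favourable outcome with 12/80 on FSH alone and 20/80 on control.

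- Section 2.7: Fisher p = 0.17, uncorrected chi-square p = 0.11. Not significant.
- Section 2.6: control advantage = 0.25 − 0.15 = 0.10. SE = √[(0.25×0.75 + 0.15×0.85)/80] = √(0.315/80) = 0.0627. One-sided 95% upper limit = 0.10 + 1.645 × 0.0627 = 0.203.

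The limit is 20.3 points, twice the margin. One section reports no significant difference; the other says non-inferiority has not been shown.

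**3. How often does this matter when FSH alone is worse by the full margin?** The rates below are assumptions, for a favourable outcome such as ongoing pregnancy. All pairs of binomial counts were enumerated, with the chi-square uncorrected. The last column is the probability that the Newcombe two-sided 90% interval for FSH alone minus control lies wholly above −10 points.

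| FSH alone vs control | n per group | Fisher p > 0.05 | Chi-square p > 0.05 | Newcombe rule shows non-inferiority |
|---|---|---|---|---|
| 5% vs 15% | 80 | 51.9% | 42.7% | 5.1% |
| 10% vs 20% | 80 | 65.1% | 57.7% | 5.2% |
| 15% vs 25% | 80 | 71.1% | 64.5% | 5.3% |
| 5% vs 15% | 25 | 92.8% | 78.7% | 5.1% |
| 10% vs 20% | 25 | 91.4% | 82.6% | 5.3% |
| 15% vs 25% | 25 | 92.2% | 85.0% | 5.4% |

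The interval rule holds its nominal 5% error. The tests of section 2.7 control no such error, because they are not tests of that null.

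**4. What can the interval rule deliver at each stage?** Under the plan's own 20% vs 15%, the Newcombe rule succeeds in 80.7% of trials at 80 per group and 40.9% at 25 per group.

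**5. Which outcome does the margin govern?** The sample size does not reveal it. The term p(1−p) summed over the arms is 0.2875 whichever arm has 20%, so a favourable outcome (20% on FSH alone) and an unfavourable one (15% on FSH alone) both give 79 per group. The Abstract and Introduction point to clinical outcome, section 2.5 makes LH peaks primary, and section 2.6 names neither. For LH peaks a higher rate is worse, so the limit that matters changes side.

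**The case against.** Several points on the other side are sound.

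- A reader might infer that the authors intend to read p > 0.05 as non-inferior. The article never says so. The only non-inferiority criterion it writes down is the confidence limit in section 2.6, and the Discussion concedes that the study is observational, cannot be conclusive and is meant to prepare for a randomised trial. What remains is that section 2.7, where the analysis is fixed, has no other decision rule.
- A reader might take "All tests will be two-sided" as the mistake. It is not: section 2.6 itself equates the one-sided 95% limit with a two-sided 90% interval. The fault lies in the chi-square and Fisher null.
- A reader might add that "All analyses will be carried out using the Intention to Treat (ITT) principle" is itself a defect in an open-label non-inferiority comparison and ask for success in a per-protocol set too. The documents do not support that as a requirement. Section 2.4.1 has group 1 receive FSH only, no crossover is described, an additional analysis set is commonly left to a fuller document, and a per-protocol set carries its own selection bias. Such an analysis could be supportive only.
- The article is condensed and its analysis plan is not shown. That would excuse a missing interval method. It does not excuse naming a method for all categorical outcomes that cannot address the hypothesis.

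**Conclusion.** The point holds: the categorical analysis written in section 2.7 cannot support the non-inferiority hypothesis for which section 2.6 sizes the study. A margin and an interval rule do exist; the defect is that they are not carried into the analysis or tied to a named outcome.

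With FSH alone truly worse by 10 points, the planned tests are non-significant in about 52% to 71% of trials (Fisher) or 43% to 65% (chi-square) at 80 per group, and in 91% to 93% or 79% to 85% at 25 per group, against about 5% false conclusions under the interval rule. These figures assume a favourable outcome and control rates of 15% to 25%. They give the frequency of non-significance, which becomes a false claim only if someone reads it as one. The mismatch between sections 2.6 and 2.7 does not depend on those rates.

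**What to change.** In section 2.7:

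1. Name the outcome and the direction to which the 10-point margin applies, and make this agree with the Abstract, the Introduction and sections 2.5 and 2.6.
2. For that outcome, report the risk difference (FSH alone minus control) with a two-sided 90% confidence interval, by Newcombe or Miettinen-Nurminen. Conclude non-inferiority only if the limit on the side unfavourable to FSH alone excludes 10 points.
3. Apply the rule at the 160-patient stage. Report the 50-subject cohort as estimation only, since the rule has about 41% power there under 20% vs 15%.
4. Keep chi-square and Fisher tests for the other categorical outcomes, and state that a non-significant result is not evidence of non-inferiority.

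No per-protocol success requirement is needed. The cost is a few sentences, with no change to the sample size or the data collected. The downside is a harder bar for the claim.

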### 2.4. Interventions

#### 2.4.1. Controlled Ovarian Hyperstimulation

All women will undergo ovarian stimulation with urinary FSH (Meriofert, IBSA Pharmaceutici, Lodi, Italy) starting on day 2 of the cycle. The starting dose of FSH will be 300 IU s.c. for the first 4 days adjusted thereafter according to the ovarian response. Monitoring of treatment will be performed via the measurement of serum estradiol concentrations and transvaginal ultrasound scans of the ovaries. Triggering of final follicle/oocyte maturation will be performed via the injection of a GnRH agonist at the single dose of 200 µg s.c. when at least 3 follicles greater than 17 mm in diameter are seen via ultrasound. Women in group 1 will receive only FSH, while women in group 2 will additionally receive a GnRH antagonist from day 6 of FSH treatment at a dose of 0.25 mg per day until the triggering day. The GnRH antagonist in group 2 will be injected each time immediately after the injection of FSH. Monitoring via ultrasound scans will begin on cycle day 7 and continue every day or every other day, depending on the examiner’s evaluation. In every scan, all follicles >10 mm in diameter (mean of two dimensions) will be recorded. From all women (both groups), blood samples (5 mL) will be obtained before the FSH injection (between 08.00 and 09.00 h) on cycle days 2 and 7 and then every other day. The last blood sample will be taken on the day of triggering regardless of the sampling frequency adopted. All blood samples will be centrifuged, and an aliquot will be stored at −20° until assayed.

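### Sections 2.5 and 2.7 run the supplementary logistic regression on different outcomes, and under 2.7 LH peaks and progesterone elevation get no multivariable analysis

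*Protocol article*

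**What the plan says.** Section 2.5 of the protocol article sets the hierarchy. "The primary outcome measures will be the frequency of LH secretory peaks during the administration of the GnRH antagonist", and progesterone elevation above 1 ng/mL is evaluated alongside. "Secondary outcome measures will be ongoing clinical pregnancy (fetal heartbeat at ultrasound) and miscarriage rates". Live birth is among the other prespecified outcomes.

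The same section makes a direct comparison of the two groups the primary analysis and then adds a regression: "We will also carry out logistic regression analysis, inserting variables, including demographic and IVF cycle characteristics". Its purpose is to "reveal potential independent predictors that could potentially contribute to the change in the primary outcomes and live birth rate".

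Section 2.7 describes the regression again: "Logistic regression analysis will be performed to determine the potential predictors of clinical pregnancy, miscarriage and live birth rates using the Enter method". For categorical variables in general it gives the chi-square and Fisher's exact tests.

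Three other places bear on the point:
- Section 2.3 allocates women 1:1 by the order in which they enter each Unit, and both women and gynecologists know which protocol is used.
- The Discussion says: "we admit that this is an observational study that will carry the associated biases a priori".
- Section 2.4.1 takes blood from all women before the FSH injection, "on cycle days 2 and 7 and then every other day". FSH starts on cycle day 2, so that sample precedes treatment.

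**The concern.** The article fixes the outcomes of the regression twice, and differently. This is not a detail deferred to a fuller plan, because both statements are explicit and cannot both be the full list. Until they are reconciled, the choice of modelled outcomes can be made after the data are seen.

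The difference also falls on the outcomes that matter most. If section 2.7 governs, LH peaks and progesterone elevation are analysed only by a crude test, while the regression goes to outcomes that arise in recipients after frozen transfer. With open allocation by order of entry, and bias conceded in the Discussion, readers will want to know whether the LH result survives allowance for pre-treatment differences between donors. Section 2.7 provides no analysis that would show this.

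**Working it through.** **1. The two outcome lists side by side**

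| Outcome | Status in 2.5 | Modelled under 2.5 | Modelled under 2.7 |
|---|---|---|---|
| LH peaks | primary | yes | no |
| Progesterone elevation | evaluated with the primary | yes, if counted among the primary outcomes | no |
| Clinical pregnancy | secondary | no | yes |
| Miscarriage | secondary | no | yes |
| Live birth | other prespecified | yes | yes |

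Live birth is the only common entry.

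**2. What each section leaves for LH peaks**

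- Under 2.5: a direct group comparison plus a supplementary model.
- Under 2.7: chi-square or Fisher's exact test only.

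The main comparison is therefore crude either way. What 2.7 loses is the supplementary model.

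**3. The plan's own sample size**

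Inputs from section 2.6: 20% against 15%, a limit of 10 points, one-sided 5% and 80% power. With the unpooled normal approximation:

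n per group = (1.645 + 0.842)² × (0.20 × 0.80 + 0.15 × 0.85) / (0.05 + 0.10)² = 6.18 × 0.2875 / 0.0225 ≈ 79

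This gives 158 in total against the stated 160, so the figure reproduces. Adding outcomes to the regression does not change it.

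**4. How much a model for LH peaks could carry**

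Section 2.6 does not say which outcome its rates describe. Assuming that they applied to LH peaks:

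- Pilot, 25 per group: 25 × 0.20 + 25 × 0.15 = 5 + 3.75 = 8.75 events.
- Full study, 80 per group: 80 × 0.20 + 80 × 0.15 = 16 + 12 = 28 events.

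As a range, take the 20% that the Discussion reports for surges in stimulated cycles as the FSH-alone rate, and the 8% to 35% that the Introduction reports for peaks under an antagonist. These sources may not use this study's threshold of 10 IU/L.

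- Pilot: 25 × (0.20 + 0.08) = 7 to 25 × (0.20 + 0.35) = 13.75 events.
- Full study: 80 × 0.28 = 22.4 to 80 × 0.55 = 44 events.

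A model with group and one covariate has two parameters besides the intercept. On the section 2.6 rates that is 8.75 / 2 ≈ 4.4 events per parameter in the pilot and 28 / 2 = 14 in the full study. Indicators for the five recruiting Units would add four parameters, giving 8.75 / 6 ≈ 1.5 and 28 / 6 ≈ 4.7. Entering an open set of demographic and cycle variables all at once is therefore not workable for LH peaks.

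The documents give no rate for progesterone elevation, so no count is shown for it.

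**The case against.** The strongest reply is that little turns on the discrepancy. Section 2.5 describes a search for predictors, does not speak of adjustment, and does not say that group is in the model. Aligning the lists would leave the primary estimate as it is. The non-inferiority hypothesis in the Abstract and Introduction concerns clinical outcomes, so modelling pregnancy, miscarriage and live birth is reasonable in itself. The first cohort is a pilot, and the Discussion disclaims definite conclusions.

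All of this stands, and it rules out three stronger readings that a reader might infer:

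- *That 2.5 promises an adjusted primary analysis which 2.7 withdraws.* The text does not support this. The primary comparison is crude under both sections.
- *That a baseline LH imbalance biases the crude result by a known amount.* The documents give no relation between day 2 LH and later peaks, and the Discussion stresses that surges cannot be predicted. Chance imbalance is in any case already part of the crude standard error. Systematic imbalance from the allocation method is the real worry, and the documents do not allow it to be quantified.
- *That such a shift can be judged against the 10-point limit in section 2.6.* That section names no outcome, and it treats the higher rate as favourable, which does not fit LH peaks.

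The reply does not remove the conflict between the lists, or the absence under 2.7 of any multivariable analysis of the primary outcome.

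**Conclusion.** The point holds in a limited form. The two sections contradict each other on which outcomes are modelled, agreeing only on live birth. Following section 2.7 leaves LH peaks and progesterone elevation with a crude test alone, in an open study that allocates by order of entry and concedes observational bias. This affects a supplementary analysis and leaves the primary estimate unchanged.

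No size of bias can be given. The event counts (about 9 in the pilot and 28 in 160 women) rest on applying the section 2.6 rates to LH peaks. They show only that the model must be very small. The correction is worth making because it is cheap and gives some protection against confounding. A model this small cannot remove confounding through factors that it does not contain.

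**What to change.** Use one list of modelled outcomes in sections 2.5 and 2.7, and include LH peaks and progesterone elevation in it. State that allocated group is in the model.

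Replace the open set of demographic and cycle characteristics with a very short prespecified set of pre-treatment variables, for example the cycle day 2 value of the same hormone. Cycle characteristics that arise after allocation, such as total FSH dose (itself listed as an outcome in 2.5), should not be used as covariates for the group effect.

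Report the adjusted group effect with its interval beside the crude comparison. Firth-penalised logistic regression is one suitable small-sample option; the choice of method and covariate is the authors' to make.

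The cost is a few lines of text and one extra model per outcome, which will be imprecise, above all in the pilot. The day 2 sample is already drawn and samples are stored, so at most one additional assay on stored serum is needed. The stated sample size is unaffected.
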